### Eligibility criteria

The trial population consists of patients with COPD who already use the telehealth system.

#### Inclusion criteria

Both men and women ≥18 years are qualified for inclusion. Furthermore, the participants must be diagnosed with COPD at any stage (no restrictions regarding the diagnostic period). The participants must also have a fixed residence in Aalborg Municipality.

#### Exclusion criteria

Participants are excluded if they are unable to monitor their vital signs or unable to complete study questionnaires.

### Recruitment

The recruitment takes place in Aalborg Municipality. Specialized COPD community nurses identify eligible participants prior to randomization (Fig. 2). Subsequently, researchers will contact the participants to give them further information about the trial, answer potential questions, and guide them regarding the written consent form. A written consent form and questionnaires will be sent to eligible participants after receiving oral consent. If the participants still wish to participate in the trial, they will return the questionnaires and the written consent form via mail using a second pre-stamped envelope. The researchers’ telephone numbers are stated on the questionnaires giving the participants the opportunity to receive help in answering the questionnaires.

**Fig. 2 Fig2:**
[figure not shown]
The trial procedure from identification and recruitment to outcome assessments at 6 months

### Randomization

The participants will, by a computer-generated list be allocated randomly (1:1) across two treatment arms: an intervention group (telehealth with algorithm) or to a control group (telehealth without the algorithm). The allocation sequence will be concealed until the participants are enrolled and assigned to the two groups. The randomization will not be performed until the included participants have signed informed consent and completed baseline questionnaires. Researchers at Aalborg University will generate the allocation sequence, enroll the participants, and assign the participants to their respective groups.

## Intervention

All participants in both groups are encouraged to measure and transfer oxygen saturation, blood pressure, and pulse data three times per week. However, patients are also allowed to only measure and transmit oxygen and pulse data using the pulse oximeter if measuring blood pressure causes discomfort. Generally, the participants must measure their vital signs on fixed days in the week, starting either Monday or Thursday. Two monitoring schedules will occur depending on the participants measuring day. If the participants usually measure on Monday, they must perform additional measurements Wednesday and Friday. Whereas if the participants usually measure on Thursday, they must measure the additional measurements on Saturday and Monday. Thus, all specialized COPD community nurses will receive more data they can use in assessing the participants’ conditions during the trial period. The only difference between the two groups is that the specialized COPD community nurses monitoring the intervention group are aided by the COPD prediction algorithm, and the specialized COPD community nurses monitoring the control group are monitoring solely based on their professional opinion and the alarms implemented in the current telehealth system. The participants will be unaware of their group allocation. The specialized COPD community nurses will not be blinded. However, they are instructed not to tell the participants about their group allocation.

### Intervention group

Participants in the intervention group will receive the general offer of the telehealth intervention including the telehealth system with the implemented COPD prediction algorithm. The COPD prediction algorithm uses weekly measurements of pulse, oxygen saturation, and blood pressure. The algorithm alerts the specialized COPD community nurses based on the probability of exacerbation within the next three days, which is estimated by logistic regression [40]. The alarm will be implemented in the telehealth platform that the nurses are already used to and will be positioned next to already existing alarms (e.g. “low values of blood pressure” or “high values of pulse”). Prior to the trial, the specialized COPD community nurses will receive training in the extended monitoring and to the addition of the new alarm. All alarms, including the COPD prediction algorithm alarm, are decision support for the specialized COPD community nurses while inspecting data and assessing the participants’ situation. The specialized COPD community nurses solely decide whether to contact the participants and/or their general practitioner.

Depending on how often the patients measure the various physiological parameters, the algorithm will predict risk of exacerbation based on one of the following two scenarios:

*Scenario 1:* The COPD prediction algorithm uses all three physiological parameters, if the patient has three weekly measurements of both pulse, oxygen saturation, and blood pressure. In this case, the COPD prediction alarm is based on the following:
Pulse: The average of the measurements from the last weekOxygen saturation: The variance of the measurements from the last 2 weeksDiastolic blood pressure: The variance of the measurements from the last week

*Scenario 2*: The COPD prediction algorithm uses only two physiological parameters, if the patient only has three weekly measurements of pulse and oxygen saturation. This is due to insufficient predictive information at less than three weekly blood pressure measurements. In this case, the COPD prediction alarm is based on the following:
Pulse: The average of the measurements from the last weekOxygen saturation: The variance of the measurements from the last 2 weeks

### Control group

Participants in the control group will continue with the general offer of the telehealth intervention without the COPD prediction algorithm. These participants are instructed to perform the same frequency of measurements as the intervention group.

### Measures to ensure minimal loss to follow up

A few measures will be taken to ensure minimal loss to follow-up. First, the specialized COPD community nurses are in contact will the participants continuously throughout the trial as part of the telehealth intervention. If the specialized COPD community nurses observe that a participant misses several measurements, he/she will contact the participant per telephone and encourage the participant to keep performing the additional measurements. If a participant is unable to return the questionnaires by mail, a researcher will pick up the letter at the participant’s home address to ensure complete follow-up.

### Criteria for discontinuation

No risks are expected to be linked to participation in the trial. On the contrary, it is expected that the quality of the telemonitoring will be increased due to the increased attention and data. However, should any adverse events occur, they will be recorded in the trial master file in REDCap with information on whether the primary investigator attributes association with the trial. Participants can always withdraw consent and will then be excluded from the trial.

### Outcomes

This study has one primary outcome, two secondary outcomes, and five explorative outcomes.

#### Primary outcome

The primary outcome is the between-group difference in the number of observed exacerbations defined as an all-cause acute hospitalization from baseline to follow-up. The trial hypothesizes that integrating a COPD prediction algorithm into the telehealth system will lead to a significantly lower number of exacerbations through early identification and timely preventive treatment

#### Secondary outcomes

The secondary outcomes include:
The change in health-related quality of life (HRQoL) using the 12-item Short Form Health Survey (version 2) (SF-12v2) [46] and the EuroQol-5 Dimension Questionnaire (EQ-5D-5L) [47] at the individual level from baseline to follow-up at 6 months. The trial hypothesizes that the difference in HRQoL from baseline to follow-up in both groups decrease since the participants have lived 6 months longer with COPD. However, it is expected that the decrease in HRQoL will be lower for the intervention group compared to the control group. Both questionnaires have previously been validated in the Danish population [48–50].The incremental cost-effectiveness ratio or ICER measured as the total cost per quality-adjusted life years (QALY) gained for the cost categories included in the study from baseline to follow-up at 6 months. It is hypothesized that the cost of hospital contacts will decrease, but it is unknown whether this cost is offset by an increase in other cost categories such as community care

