### Statistical methods

Overall, the statistical methods will follow an intention-to-treat principle [54]. Results from the trial will be presented in accordance with the Consolidated Standards of Reporting Trials (CONSORT) for randomized trial guidelines [55] as well as the Consolidated Health Economic Evaluation Reporting Standards (CHEERS) [56]. Missing data will be subject to multiple imputation [57]. If there is a need for an adjustment of the participants’ baseline characteristics due to differences among the two groups, this will be performed.

To assess the primary outcome, Poisson regression with exponentiated coefficients will be used to produce incidence rate ratios. In assessing HRQoL, generalized linear models [58] will be used to model EQ-5D-5L and the two SF12v2 summary scores; the physical component score (PCS-12) and the mental component score (MCS-12). To assess the secondary outcome of cost-effectiveness, an ICER point estimate will be calculated after 6 months follow-up. The ICER is defined as the difference in the average costs between the two alternatives divided by the difference in average effectiveness between the same alternatives [59]. For the ICER calculation, the effectiveness for both alternatives is assessed based on the utility scores from the EQ-5D-5L questionnaire, with Danish societal weights that are unpublished but under journal peer review [50]. With the help of information on within-trial survival time, QALYs can then be elucidated with linear interpolation of utility scores between baseline and follow-up at six months as the area under this curve [59].

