In assessing base-case total costs for both alternatives, this trial adopts a healthcare sector perspective, meaning that the following cost categories are included: additional costs in implementing the algorithm, in- and outpatient hospital costs, medication costs, costs from visiting primary care and general practitioners in particular, community care costs associated with home nurse visits, individual care, and practical help as well as rehabilitation activities in the municipalities. Treatment effects for effectiveness and costs will be calculated separately by applying generalized linear models [58] and will be reported both as an unadjusted estimate and as an estimate that controls for meaningful baseline differences. Finally, the economic evaluation will nuance base-case results by applying both one-way and probabilistic sensitivity analysis (PSA) to allow decision-makers to evaluate the impact of parameter uncertainty that might occur during the trial period on cost-effectiveness at a range of willingness-to-pay levels for an improvement in QALYs [60, 61].

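### Baseline adjustment of the HRQoL and QALY analyses hangs on observed imbalance instead of being fixed, and the plan does not say which QALY difference feeds the ICER

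*Protocol article*

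**What the plan says.** All references are to the protocol article.

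- **Secondary outcomes** defines the HRQoL outcome as "The change in health-related quality of life (HRQoL) using the 12-item Short Form Health Survey (version 2) (SF-12v2" and EQ-5D-5L, measured "at the individual level from baseline to follow-up at 6 months".
- **Statistical methods**, on the HRQoL model: "generalized linear models [58] will be used to model EQ-5D-5L and the two SF12v2 summary scores". No covariates are listed, and the text does not say that the baseline score is left out.
- **Statistical methods**, general rule: "If there is a need for an adjustment of the participants’ baseline characteristics due to differences among the two groups, this will be performed".
- **Statistical methods**, on QALYs: "QALYs can then be elucidated with linear interpolation of utility scores between baseline and follow-up at six months as the area under this curve". The ICER is the ratio of the differences in average cost and average effectiveness.
- **Statistical methods**, in the paragraph on costs: effects on effectiveness and costs "will be reported both as an unadjusted estimate and as an estimate that controls for meaningful baseline differences". Neither estimate is designated as the one behind the ICER.
- **Randomization** and **Table 1**: the baseline questionnaires are completed before allocation, and EQ-5D-5L and SF-12v2 are measured only at baseline and 6 months.

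**The concern.** The article does more than stay silent on covariates. It states a rule, and the rule depends on the data: adjust if the groups turn out to differ. Two things follow.

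First, the baseline score is the covariate most likely to predict the 6-month score, and its value for precision does not depend on the arms differing visibly. A rule triggered by imbalance can drop it exactly when the arms look balanced.

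Second, the QALY is where this costs most. With two measurement points, half of a survivor's QALY is a utility recorded before randomisation, which treatment cannot change. An ordinary chance baseline difference passes into the QALY contrast and, if the unadjusted difference is used, into the denominator of the ICER. Choosing between adjusted and unadjusted after seeing the baseline table also leaves an analyst's choice open in a trial whose outcome assessment is not blinded (Study design).

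**Working it through.** **Inputs.** The article gives no SD, correlation or design figure for HRQoL or QALYs, so there is no stated figure to reproduce on this point. From the article: two measurement times, 1:1 allocation, and 85 per group (Sample size), used here only as the number analysed per arm. Assumptions: equal SD s at both times, correlation r of 0.3, 0.5 or 0.7, linear models with identity link, and survivors with complete data.

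**Does the change score itself cost precision?** No. Regressing change on arm plus baseline gives the same arm effect as regressing the 6-month score on arm plus baseline; in simulation the two agreed to about 1e-15. Only leaving the baseline out of the model costs anything.

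**HRQoL, variance per participant**
- Change score without baseline: 2s²(1−r)
- With baseline as covariate: s²(1−r²)
- Variance reduction: 1 − (1+r)/2 = (1−r)/2

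**QALY.** Over half a year the straight-line area is 0.5 × (U0+U1)/2 = 0.25(U0+U1).
- Without baseline: s²(1+r)/8
- With baseline utility as covariate: s²(1−r²)/16
- Variance reduction: 1 − (1−r)/2 = (1+r)/2

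| r | HRQoL variance reduction | HRQoL SE ratio, without/with | QALY variance reduction | QALY SE ratio, without/with |
|---|---|---|---|---|
| 0.3 | 35% | 1.24 | 65% | 1.69 |
| 0.5 | 25% | 1.15 | 75% | 2.00 |
| 0.7 | 15% | 1.08 | 85% | 2.58 |

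A simulation with 85 per arm and 3,000 runs gave 36%, 26% and 14% for HRQoL and 66%, 76% and 84% for QALYs. In power terms, where the HRQoL analysis with the covariate has 80% power, the change score without it has 62%, 68% and 73%.

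**Sensitivity.** With r from 0.2 to 0.9 and equal SDs, the variance reductions run from 40% down to 5% (HRQoL) and from 60% up to 95% (QALY). With r from 0.3 to 0.7 and a follow-up to baseline SD ratio of 0.8 to 1.2, they span about 3% to 50% and 58% to 88%.

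**Would the trigger catch a difference that matters?** Assume a utility SD of 0.2.
- The SE of the baseline difference is 0.2 × √(2/85) = 0.031.
- A chance difference of one SE has a two-sided p of about 0.32, so it would hardly prompt adjustment.
- At r = 0.5 it shifts the expected unadjusted QALY contrast by 0.25 × (1+0.5) × 0.031 = 0.0115.
- A true 6-month utility gain of 0.05 is worth 0.25 × 0.05 = 0.0125 QALY, about the same size.
- With that true gain, the QALY difference has the wrong sign in about 17% of trials unadjusted (SE 0.0133) and about 3% adjusted (SE 0.0066).
- The same imbalance moves the unadjusted EQ-5D change contrast the other way, by (1−0.5) × 0.031 = 0.015.

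**The case against.** The strongest reply is that the article never says the baseline score is omitted. It names the scores to be modelled, lists no covariates, and a covariate list is commonly left to the SAP. It also plans an adjusted estimate for effectiveness; if baseline EQ-5D-5L is among the covariates, the QALY loss in that estimate is zero. Under randomisation, both the change-score contrast and the unadjusted area contrast are unbiased, so what is left is efficiency in secondary outcomes.

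Most of this stands. A reader might infer that defining HRQoL as change, or the QALY as an area, is itself the fault, and that 15% to 35% and 65% to 85% of the precision is already lost. The documents do not support that. The change score is harmless once its baseline is in the model, the area is an ordinary construction with two time points, and the percentages rest on an assumed correlation and apply only to an analysis without the baseline score.

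What the reply does not remove is the rule the article does state. Adjustment depends on need arising from group differences, or on differences being meaningful. No baseline HRQoL score is guaranteed a place under either wording, and the choice of estimate for the ICER is open. An SAP that fixed the covariate would be replacing this rule, not filling a gap.

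**Conclusion.** The point holds as one about data-dependent adjustment. As written, the EQ-5D-5L, PCS-12, MCS-12 and QALY contrasts can be estimated without the baseline score when the arms look balanced, and the QALY difference behind the ICER is undefined. The cost is precision, not bias. With equal SDs and r of 0.3 to 0.7, an HRQoL analysis that omits the baseline has an SE 24% to 8% larger; a QALY analysis that omits it has an SE 1.7 to 2.6 times as large. The QALY and ICER part is the more serious; the HRQoL part is modest. The correlation, the equal SDs and the utility SD of 0.2 are assumptions. Deaths and imputed values would add variance that the baseline score does not remove, so the realised gain for QALYs could be smaller.

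**What to change.** In Statistical methods, replace the conditional rule for these outcomes with a fixed one, for example:

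- EQ-5D-5L, PCS-12 and MCS-12 are each modelled on arm plus the participant's own baseline value of that score, in every case. With an identity link, the 6-month score and the change score give the same arm effect, so the outcome definition can stay.
- QALYs are modelled on arm plus baseline EQ-5D-5L utility, in every case.
- The base-case ICER uses that adjusted QALY difference; the unadjusted estimate is reported as supportive.

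The cost is a few sentences of wording. The baseline scores are already collected before randomisation, so no new data, visits or participants are needed.

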#### Explorative outcomes

To assess the participants’ health literacy level at baseline using the European Health Literacy Survey Questionnaire (HLS-EU-Q16) [51], supported by further assessment with the Danish Test of Functional Health Literacy in Adults (the Danish TOFHLA) [52] during the trial period to examine whether the effect of the COPD prediction algorithm is similar in patients with COPD, regardless of health literacy levelTo examine whether the specialized COPD community nurse’s estimate of the individual participant’s level of health literacy influences the effect of the COPD prediction algorithmTo evaluate the specialized COPD community nurses’ experiences with the usability of the COPD prediction algorithm using interviewsTo evaluate the participants’ experiences with the usability of the telehealth system after trial completion using the Danish Telehealth Usability Questionnaire (D-TUQ) questionnaire [53]To evaluate the participants’ experiences with data ethical aspects after trial completion using qualitative research interviews

The SF-12v2, the EQ-5D-5L, HLS-EU-Q16, and questions about demographic characteristics are sent to the participants by letter at baseline. The D-TUQ, SF-12v2, and EQ-5D-5L are sent at follow-up (Table 1). If a participant is unable to return the questionnaires by mail, a research assistant will pick up the letter at the participant’s address to promote complete follow-up.

**Table 1 Tab1:** An overview of the questionnaires that the participants receive at baseline, intermediate, and after 6 months follow-up

Name of the questionnaire	Time point for each outcome
The 12-item Short Form Health Survey (version 2)	Baseline, 6 months follow-up
The EuroQol 5-Dimension questionnaire	Baseline, 6 months follow-up
The European Health Literacy Survey Questionnaire	Baseline
Questions about demographic characteristics	Baseline
The Danish Test of Functional Health Literacy in Adults The	Intermediate
Danish Telehealth Usability Questionnaire	6 months follow-up

During the trial period, the level of health literacy will be assessed further with the Danish TOFHLA. Additionally, the COPD community nurses will be asked to provide an estimate of the individual level of health literacy among the participants with COPD [52].

Qualitative research interviews will also be conducted with selected participants and/or specialized COPD community nurses during and after trial completion, which will focus on data ethical aspects and user experiences of the telehealth system.

After trial completion, data is extracted comprising data from OpenTeleHealth (physical measurements) and relevant registers (all hospital contacts, all prescribed medicine, all contacts in primary sector, and all social sector contacts) in order to compare the number of exacerbations and the incremental-cost effectiveness ratio from baseline to 6 months follow-up between the intervention- and control group. All data will be stored in REDCap (Research Electronic Data Capture). Only researchers from Aalborg University will have access to the trial dataset.

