The HLS-EU-Q16 and the Danish TOFHLA provide an individual health literacy score. The HLS-EU-Q16 provides a score ranging from zero (inadequate) to 50 (excellent) and divides the participants into four (HL) groups on this basis. The Danish TOFHLA provides a score ranging from zero (inadequate) to 100 (adequate) and divides the participants into three (HL) groups on this basis. It will be examined whether the division into different groups is similar regardless of health literacy being assessed with the HLS-EU-Q16 or the Danish TOFHLA. One-Way ANOVA will be used to test pre (baseline)-post (follow-up) between-HL-group (as measured with the HLS-EU-Q16) differences in the number of exacerbations. One-Way ANOVA will also be used to test pre (baseline)–post (follow-up) between-HL-group (as measured with the Danish TOFHLA) differences in the number of exacerbations. Furthermore, the specialized COPD community nurses estimate an individual health literacy score among their COPD patients ranging from zero (inadequate) to 10 (adequate) based on their professional judgment. This individual health literacy score provided by the specialized COPD community nurses divides the participants into three (HL) groups. One-Way ANOVA will be used to test pre (baseline)–post (follow-up) between-HL-group differences in the number of exacerbations. It should be noted that the individual health literacy score provided by the specialized COPD community nurses will be compared to the scores obtained with both the HLS-EU-Q16 and the Danish TOFHLA to examine if their professional judgment with regards to health literacy is in line with the standardized scores provided by these tests.

Descriptive statistics will be conducted for the D-TUQ by examining the range, median, and frequency of responses for each item including plots. The questionnaire check marks are listed on a Likert scale ranging from one (disagree) to seven (agree) indicating each participants’ level of agreement with the questions.

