### Sample size

The sample size calculation is based on the primary outcome. It is assumed that the control group experience an average of two exacerbations, and the intervention group experienced one exacerbation during the trial period from baseline to the 6-months follow-up. With a power of 90%, a variance of two exacerbations for both groups, a two-sided significance level of 0.05, the required sample size is estimated to be at least 85 participants in each group [62]. Based on experience from the original large-scale trial, TeleCare North [34], a loss to follow-up of 15% in each group is expected. Therefore, the total required sample size in each arm is the estimated to be approximately 100 participants.

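### The planned health-literacy ANOVAs leave out the trial arm, so they cannot show whether the algorithm's effect is similar across literacy levels; and a non-significant arm-by-literacy test would not show similarity either

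*Protocol article*

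**What the plan says.** Under Explorative outcomes, the protocol article sets out to examine "whether the effect of the COPD prediction algorithm is similar in patients with COPD, regardless of health literacy" level. Literacy is measured with the HLS-EU-Q16 at baseline and the Danish TOFHLA during the trial. A second explorative outcome asks whether the nurses' own estimate of a participant's literacy influences the algorithm's effect. Both questions concern effect modification.

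Statistical methods names the analysis. For each of the three literacy measures (four groups for the HLS-EU-Q16, three for the TOFHLA, three for the nurse score), a one-way ANOVA tests pre-post "differences in the number of exacerbations" between literacy groups. The trial arm does not appear in these tests. No estimate or interval for a difference in effect between literacy levels is named.

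Under Sample size: "The sample size calculation is based on the primary outcome". It assumes that "the control group experience an average of two exacerbations, and the intervention group experienced one exacerbation" over six months, with "a variance of two exacerbations for both groups" and "a two-sided significance level of 0.05". The result is that "the required sample size is estimated to be at least 85 participants in each group", or about 100 after 15% loss to follow-up.

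**The concern.** A one-way ANOVA with literacy group as its only factor asks whether exacerbation counts differ by literacy. The stated question is whether the difference between arms varies by literacy. One can be true without the other.

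Adding the arm leaves a second problem. The question is worded as similarity, while the tool is a significance test for a difference in a trial sized only for its main effect. Failing to find a difference is then weak evidence of similarity. At stake is an equity statement, that patients with low literacy gain as much from the algorithm as others, which readers may take as reassurance although the analysis cannot supply it.

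**Working it through.** **1. What the ANOVA compares.** Let C and T be the mean counts in control and intervention, with subscripts for two literacy groups and 1:1 allocation within each. The one-way ANOVA compares (C₁+T₁)/2 with (C₂+T₂)/2. Effect modification compares T₁−C₁ with T₂−C₂, or T₁/C₁ with T₂/C₂ on the rate-ratio scale of the primary analysis. Two hypothetical cases built on the plan's means of 2 and 1:

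- Group 1 goes from 2 to 1 and group 2 from 1.5 to 1.5. Both literacy means are 1.5, so the ANOVA sees nothing, yet the rate ratios are 0.5 and 1.
- Group 1 goes from 2 to 1 and group 2 from 1 to 0.5. The literacy means are 1.5 and 0.75, so the ANOVA sees a difference, yet both rate ratios are 0.5.

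Subtracting a pre-trial count that is equal in all cells changes neither case.

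**2. The plan's own sample size.** n per arm = 2(z₀.₉₇₅ + z₀.₉₀)² × variance / difference², with z values 1.960 and 1.282 and a difference of 1.

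- SD 2 (variance 4): 2 × 10.507 × 4 = 84.06, rounded up to 85. This is the stated figure, and 85/0.85 = 100.
- Literal variance 2: 2 × 10.507 × 2 = 42.03, rounded up to 43. This is not the stated figure.

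SD 2 is therefore the working value below, and literal variance 2 is shown as the alternative.

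**3. Power of an arm-by-literacy test, two equal groups** (difference scale, equal variance in all cells). With n per arm, each cell holds n/2 patients, so SE = SD × √(4/(n/2)) and power ≈ Φ(d/SE − 1.96). Here d is the difference in effect between the groups; d = 1 equals the whole planned effect.

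| SD | n per arm | SE | power, d = 1 | power, d = 2 |
|---|---|---|---|---|
| 2 | 85 | 0.614 | 37% | 90% |
| 2 | 100 | 0.566 | 42% | 94% |
| √2 | 85 | 0.434 | 64% | over 99% |
| √2 | 100 | 0.400 | 70% | over 99% |

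Unequal groups lower the power. At SD 2, 85 per arm and d = 1, it is 32% for a 30/70 split and 26% for a 20/80 split.

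**4. Three or four equal groups, as planned.** Noncentral F with k−1 and 2n−2k degrees of freedom, effects evenly spaced over a range d, and λ = Σ (n/2k)(eᵢ − ē)²/SD². For k = 3, n = 85, SD 2 and d = 1: λ = 14.17 × 0.5/4 = 1.77.

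| SD, range of effects | 3 groups, 85 to 100 per arm | 4 groups, 85 to 100 per arm |
|---|---|---|
| SD 2, range 1 | 20–23% | 15–17% |
| SD 2, range 2 | 65–73% | 50–58% |
| SD √2, range 1 | 37–42% | 26–31% |

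**5. Rate-ratio scale, two equal groups.** Assume negative-binomial counts with control mean 2 and variance m + 0.5m² (SD 2 in controls). A cell's log rate then has variance (1/m + 0.5)/(n/2). At 100 per arm:

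- Ratios 0.375 v 0.625: variance sum 0.02 + 0.02 + 0.0367 + 0.026 = 0.1027, SE 0.320, |ln 0.6| = 0.511, power 36% (31% at 85).
- Ratios 0.5 v 1.0: variance sum 0.09, SE 0.30, ln 2 = 0.693, power 64% (57% at 85).
- Pure Poisson variance (no 0.5 term): 53% and 87%.

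**6. Width of the interval.** At SD 2, 85 per arm and two equal groups, the 95% half-width for the difference in effect is 1.96 × 0.614 = 1.20 exacerbations, wider than the planned effect of 1. On the ratio scale, with a true rate ratio of 0.5 in both groups, the variance sum at 100 per arm is 0.02 + 0.02 + 0.03 + 0.03 = 0.10. The interval runs from the estimate divided by exp(1.96 × 0.316) = 1.86 to the estimate times 1.86 (factor 1.96 at 85 per arm).

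**The case against.** The strongest reply is that the protocol draws no such inference. It says the question will be examined and that differences will be tested; nowhere does it say that p > 0.05 will be reported as similar. The outcome is one of five labelled explorative, sizing a trial on its primary outcome is normal, and reporting rules for exploratory subgroups can sit in an analysis plan that is not shown. All of this stands, and it keeps the point minor. It does not rescue the ANOVAs: the article itself names the test and its only factor, and that test does not address the question.

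A reader might also infer that the trial cannot detect even large inequality of effect, or that a finding of similarity would usually be false. The documents support neither.

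- **Detection.** It depends on the contrast, the variance reading, the grouping and the scale. In two equal groups at SD 2, an effect of 2 in one half and none in the other is detected 90–94% of the time. Rate ratios of 0.5 v 1.0 are detected 57–64% of the time.
- **Falsity.** The 63% miss rate (1 − 0.37) applies only if a real difference of 1 exists. If that has prior probability π, the chance that a difference exists after a non-significant result is 0.63π/(0.63π + 0.95(1−π)): 7% at π = 10%, 40% at π = 50%, and above one half only when π exceeds about 60%. The documents give no π. Low power makes the conclusion unsupported, not usually wrong.

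An equivalence margin is also hard to justify for an explorative outcome. With a half-width of 1.20, similarity within a margin of 1 could not be shown at SD 2 and 85 per arm.

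**Conclusion.** The point holds in two parts. First, the one-way ANOVAs have no arm term, so no result from them bears on whether the algorithm's effect varies with literacy. This rests on the text alone. Second, if the arm is added, a non-significant interaction still would not support similarity: at SD 2, a difference as large as the whole planned effect is missed 58–63% of the time in two equal groups and 77–85% of the time in three or four.

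The second part assumes equal literacy groups (sizes are not given), evenly spaced effects, equal cell variances on the difference scale, and SD 2 as the value that reproduces 85 per arm. With literal variance 2, the miss rate in two equal groups is about 30–36%. The primary analysis is untouched, and this is a minor improvement to an explorative outcome.

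**What to change.** In Statistical methods, replace the literacy ANOVAs with a count regression of exacerbations on arm, baseline HLS-EU-Q16 score and their interaction, on the incidence-rate-ratio scale already used for the primary outcome. Report the ratio of incidence rate ratios, per literacy level or per SD of the score, with its 95% confidence interval as an exploratory estimate. State that a non-significant interaction will not be read as similarity. The TOFHLA and nurse scores can go through the same model as supporting results, noting that both are collected during the trial. No equivalence margin is needed.

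The cost is wording and one model specification, with no extra data or patients. The downside is that the trial will probably have to report this question as unresolved.
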